### **8.4 DSMB and interim analysis**

The independent Data Safety Monitoring Board (DSMB) will ensure patient safety, receive and review interim analyses of efficacy data, provide feedback to the Steering Committee, and ensure the study follows the highest standards of ethics. The DSMB will consist of a cardiac surgeon, cardiologist and epidemiologist not affiliated with this trial. The DSMB will follow clinical events (all-cause mortality, perioperative MI, low-output syndrome, vein harvest site infections, drug adverse events/intolerance) for both the surgical and pharmacologic arms. A single interim analysis will be performed following completion of 50% of angiograms. The DSMB will recommend stopping the trial if there is an excess of MACE or if the rate of graft occlusion in a treatment group is greater than the rate of graft occlusion in a control group, with a significance of  $p < 0.001$ . As the design is factorial, one treatment modality could be stopped if the difference between groups is highly significant ( $p < 0.001$ ), and the other arm continue. A single interim analysis will be performed following completion of 50% of the follow-up angiograms, using a p value of  $< 0.001$  to preserve the 0.05 alpha level. The final analysis will be performed following completion of all angiograms. A decision to continue or stop the trial would be based on a number of factors in addition to the statistical significance of the main results, including consistency of the pattern of the data over time and an assessment of net benefit-risk ratios. At any time during the study, if safety concerns arise the DSMB chairperson will assemble a meeting of the full committee. The DSMB will make their recommendations to the steering committee after considering all the available data and any external data from relevant studies.

## 8.5 Sample size calculation

### A. SURGICAL ARM

The sample size estimation is based on the current prevalence of 1-year SVG occlusion using the conventional harvesting technique to be 20% (5,6). We consider a 30% relative risk reduction (RRR) in graft occlusion using the “no touch” technique to be a clinically important difference, consistent with RRRs reported for previous interventions to improve graft patency (antiplatelet therapy, use of statins post CABG, radial versus saphenous veins) and very conservative in terms of Souza’s clinical trial results (45,46). A sample size of 615 patients in each group will provide 80% power for a 2-tailed alpha of 0.05, to identify a RRR of 30% (20% occlusion rate in the control/ conventional harvesting group, to 14% in the experimental/”no touch” group – see Table 2a).

### B. PHARMACOLOGICAL ARM

The literature suggests that fish-oils provide a RRR of about 25% compared to placebo (54,55, 65,69). Given a two-tailed alpha of 0.05, and an estimated 30% of control patients with  $\geq 1$  graft occluded at 1-year, a sample of 540 patients in each group (fish-oil versus placebo) will provide a power of 80% to detect a RRR of 25%. A sample size of 615 patients (required for the surgical intervention) provides approximately 85% power to test the fish oil hypothesis (see Table 2b).

We anticipate that 80% of patients will undergo 1-year coronary CT angiography, which is consistent with our past trial experience (7). The primary reason that patients failed to undergo late angiography in RAPS was late withdrawal of consent in 77 patients, protocol violation in 17 patients, new contraindication precluding research angiography in 19 patients and death in 8 patients (7). To adjust for this potential loss to follow-up angiography, the corrected sample size is 769 patients in each surgical group to ensure adequate statistical power when making our conclusions for both arms of the factorial design. Thus we aim to recruit a **total of 1,550** patients for the overall study across ~50 participating sites, 10 Canadian and the remaining International. The pilot phase will recruit 50 patients from 10 sites (5 Canadian and 5 International). Pilot patients will be included in the final analysis. *While MACE between groups will be tested using the total sample size, we will only be able to detect very large differences at 1 year, as MACE is expected to be approximately 10 - 12% (6,7,17).*

**Table 2a:** Sample Size Estimates for Primary Endpoint (Surgical Arm) – 1-Year Graft Occlusion (two-tailed  $\alpha=0.05$ ,  $\beta=0.20$ )

| Control Event Rate | Relative Risk Reduction |             |                     |             |                     |             |                     |             |                     |             |
|--------------------|-------------------------|-------------|---------------------|-------------|---------------------|-------------|---------------------|-------------|---------------------|-------------|
|                    | 20%                     |             | 25%                 |             | 30%                 |             | 35%                 |             | 40%                 |             |
|                    | No-Touch Event Rate     | Sample Size | No-Touch Event Rate | Sample Size | No-Touch Event Rate | Sample Size | No-Touch Event Rate | Sample Size | No-Touch Event Rate | Sample Size |
| 15%                | 12.0%                   | 2036        | 11.25%              | 1272        | 10.5%               | 862         | 9.75%               | 617         | 9.0%                | 460         |
| 16%                | 12.8%                   | 1889        | 12.0%               | 1181        | 11.2%               | 800         | 10.4%               | 573         | 9.6%                | 427         |
| 17%                | 13.6%                   | 1759        | 12.75%              | 1100        | 11.9%               | 745         | 11.05%              | 534         | 10.2%               | 398         |
| 18%                | 14.4%                   | 1644        | 13.5%               | 1028        | 12.6%               | 697         | 11.7%               | 499         | 10.8%               | 373         |
| 19%                | 15.2%                   | 1540        | 14.25%              | 964         | 13.3%               | 654         | 12.35%              | 469         | 11.4%               | 350         |
| 20%                | 16.0%                   | 1447        | 15.0%               | 906         | 14.0%               | 615         | 13.0%               | 441         | 12.0%               | 329         |
| 21%                | 16.8%                   | 1363        | 15.75%              | 854         | 14.7%               | 579         | 13.65%              | 416         | 12.6%               | 310         |

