protective for SVG patency (OR 0.77, 95% CI 0.60 - 0.99) and serum n-3 phospholipid levels were inversely correlated with graft occlusion. In addition to these potential gains, fish-oils are low-cost, usually well tolerated, and have been used in larger clinical trials in association with other evidence-based therapies (62,63,64,66,67).

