### **3 STUDY DESIGN**

#### **3.1 Type of study**

This study is an International, multi-centre, prospective, controlled RCT using a 2x2 factorial design; involving a surgical intervention and a pharmacological intervention. For the surgical intervention, surgeons will be unblinded while patients, care providers, data collectors and outcome adjudicators will be blinded. For the pharmacologic intervention, patients, all care providers, data collectors and outcome adjudicators will be blinded. Approximately 10 Canadian and 40 International centers will participate.

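### Section 8.5 powers each factorial margin as a separate two-group trial and assumes an optimistic fish-oil effect, so the stated 80% and 85% hold only under conditions that it does not state

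*Protocol*

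**What the plan says.** Section 3.1 describes a "controlled RCT using a 2x2 factorial design; involving a surgical intervention and a pharmacological intervention". Section 8.3 compares no-touch with conventional harvesting, and fish oil with placebo, each by a chi-square test.

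Section 8.5 sizes the two comparisons separately.

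- Surgical: the control occlusion rate is 20%, tied to conventional harvesting, and falls to 14% under a 30% RRR. "A sample size of 615 patients in each group will provide 80% power for a 2-tailed alpha of 0.05".
- Fish oil: "The literature suggests that fish-oils provide a RRR of about 25% compared to placebo". With 30% of control patients having at least one occluded graft, 540 per group gives 80% power, and "A sample size of 615 patients (required for the surgical intervention) provides approximately 85% power to test the fish oil hypothesis".

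The only adjustment is for 20% of patients without 1-year angiography, which takes 615 to 769 per group and leads to the total of 1,550. Neither control rate is adjusted for the other intervention.

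The background section on fish oil (1.B.III) reports one fish-oil effect on grafts, from a 610-patient randomised trial in CABG patients: "protective for SVG patency (OR 0.77, 95% CI 0.60 - 0.99)". The other fish-oil effects given there as figures are mortality outcomes.

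**The concern.** In a 2x2 factorial analysed at the margins, half of the conventional-harvest patients take fish oil and half of the placebo patients have a no-touch graft. If the other intervention works, the event rate in each control margin is below the untreated rate. With a fixed RRR the absolute difference shrinks too, and power falls. Section 5.5 says that fish oil could act on any graft, study or non-study, so the protocol does not treat the two interventions as acting on separate events.

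The planning rates look like untreated rates. Section 8.5 ties the 20% to conventional harvesting. The 30% equals the share of patients with an occluded vein graft in the single-centre imaging trial cited in section 1.A.I, and 30% divided by the 1.5 vein grafts per patient expected in section 5.4 gives 20%.

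The second issue is the size of the fish-oil effect. An odds ratio of 0.77 is a smaller risk reduction than 25% at any control rate, so the fish-oil power is sensitive to which effect is believed.

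Section 8.5 presents the sample size as giving adequate power for both arms of the factorial. A reader of a null fish-oil result would weigh it against the stated 85%.

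**Working it through.** **Formula.** Two-sided α = 0.05, n per group, pooled variance under the null, no continuity correction:

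power = Φ{ [ |p1 − p2| − 1.96·√(2p̄(1 − p̄)/n) ] / √[ (p1(1 − p1) + p2(1 − p2))/n ] }, with p̄ = (p1 + p2)/2.

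**Step 1: reproduce section 8.5.**

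- Surgical, 20% vs 14%, n = 615: (0.06 − 1.96 × 0.02142)/0.02135 = 0.844, power 80.1%. Stated: 80%.
- Fish oil, 30% vs 22.5%, n = 615: (0.075 − 1.96 × 0.02509)/0.02500 = 1.033, power 84.9%. Stated: about 85%. The 540 per group for 80% also reproduces.
- Attrition: 615/0.8 = 769.

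**Step 2: marginal rates.** With 1:1 allocation and no interaction on the relative-risk scale, both rates in a comparison are multiplied by 1 − RRR_other/2.

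*Surgical*, with fish oil lowering study-graft occlusion by 25% (factor 0.875): 20% becomes 17.5% and 14% becomes 12.25%. Then (0.0525 − 1.96 × 0.02029)/0.02024 = 0.629, power 73.5%; 80% would need 720 per group. If fish oil acts only at an odds ratio of 0.77, its RRR at a 20% control rate is 19.3%, the factor is 0.904, and surgical power is 75.1%.

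*Fish oil.* The protocol assumes a 30% no-touch effect on study vein grafts and gives no figure for its effect on the proportion of patients with any occluded graft. A range is therefore needed:

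| Assumed no-touch reduction in patient-level rate | Marginal rates | Power, n = 615 |
|---|---|---|
| 10% | 28.5% vs 21.4% | 82.4% |
| 20% | 27.0% vs 20.3% | 79.7% |
| 30% | 25.5% vs 19.1% | 76.6% |

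The 1,550 total gives 775 × 0.8 = 620 evaluable per group, which adds about 0.3 points.

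**Step 3: untreated rates that would restore the stated powers.** The margin must equal the planning rate: 20%/0.875 = 22.9% surgical, and 30%/0.85 = 35.3% fish oil (at the 30% patient-level no-touch effect).

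**Step 4: the odds ratio as an RRR.** At a 30% control rate the odds are 0.30/0.70 = 0.4286. Multiplying by 0.77 gives 0.330, a risk of 0.330/1.330 = 24.8%. The RRR is 1 − 24.8/30 = 17.3%.

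- Power at n = 615 for 30% vs 24.8%: 53.2%; 80% would need about 1,160 per group.
- With the 25.5% margin as well (25.5% vs 20.9%): 48.8%.
- The RRR implied by an odds ratio of 0.77 is 19.3% at a 20% control rate and 14.1% at 45%. It approaches 23% only as the rate tends to zero.
- Conversely, 30% vs 22.5% is an odds ratio of (0.225/0.775)/(0.30/0.70) = 0.68.

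**The case against.** There is a substantial case on the other side.

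- *Nothing in 8.5 is miscalculated.* This stands. The issue lies in the inputs and in conditions left unstated.
- *The true untreated rates may be higher.* This stands. Section 1.A.I cites a large trial with 25% of vein grafts and 45% of patients occluded. On those rates the diluted powers would be about 84% (21.9% vs 15.3%) and 95% (38.3% vs 28.7%). The same section cites 13% of study vein grafts in another trial, so the net direction is uncertain. A reader might infer that 80% and 85% hold only if the other intervention is inert. That is too strong, because untreated rates of about 23% and 35% restore them as well.
- *A single diluted fish-oil figure of 77% goes beyond the protocol.* This stands. It needs a 30% patient-level no-touch effect. The 30% is assumed for study vein grafts, section 5.1 only encourages the same technique for other vein grafts, and the fish-oil endpoint also counts arterial grafts. A range is the honest statement.
- *The calculations leave out cardiovascular death, which is part of the primary outcome.* This stands. As an illustration, adding 2 points (section 1.B.IV puts CABG mortality below 2%) gives 78.2% surgical and 80.0% fish oil on the diluted margins if the full RRR applies to deaths, and 69.1% and 74.1% if deaths are unaffected. Neither variant restores the stated figures.
- *Tables 2a and 2b already show the sensitivity.* Partly. Table 2a requires 697 per group at 18% and 745 at 17% for a 30% RRR, but nothing tells the reader that the factorial moves the trial to those rows.
- *The 25% RRR is contradicted by the odds ratio.* A reader might infer this, and the documents do not support it. The planned effect, an odds ratio of about 0.68, lies inside 0.60 to 0.99. Section 8.5 attributes the 25% to four references. The 0.77 may also be per graft, so converting it at a patient-level rate is an assumption.

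**Conclusion.** The point holds in conditional form. If 20% and 30% are untreated rates and both interventions work as the protocol assumes, surgical power at 615 per group is about 73.5%, or about 75% if fish oil acts at an odds ratio of 0.77, against the stated 80%. Fish-oil power is then about 77% to 82%, against the stated 85%, for a patient-level no-touch effect from 30% down to 10%. These figures assume no interaction on the relative-risk scale and leave out the death component.

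Separately, the 25% fish-oil RRR is optimistic against the one graft-patency effect reported, though not excluded by it. At an RRR of about 17% the power is roughly 50%: 53% at a 30% control rate and 49% on the 25.5% margin.

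The stated powers should be restated, because section 8.5 gives them without the conditions on which they rest.

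**What to change.** Keep the sample size. In section 8.5, with a note under Tables 2a and 2b:

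1. State that 80% and about 85% apply if 20% and 30% are the marginal control rates. That is so if the other intervention has no effect, or if the untreated rates are about 23% and 35%.
2. State that otherwise, under the protocol's joint hypotheses, power at 615 per group is about 73% to 75% surgical and 77% to 82% fish oil, and say that the fish-oil range reflects an assumed patient-level no-touch effect of 30% to 10%.
3. Add a sensitivity figure for fish oil at an RRR of about 17%, the value implied by an odds ratio of 0.77 at a 30% control rate: roughly 50% power. Note that this odds ratio may be per graft.
4. Note that the planning rates leave out the cardiovascular-death component of the primary outcome.

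The cost is rewording and a less favourable stated power. No extra patients, procedures or design changes are needed.

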**CONFIDENTIAL**  
SUPERIOR SVG – 2011-06-13

|            |       |             |        |            |       |            |        |            |       |            |
|------------|-------|-------------|--------|------------|-------|------------|--------|------------|-------|------------|
| 22% | 17.6% | 1287 | 16.5%  | 806 | 15.4% | 547 | 14.3%  | 393 | 13.2% | 293 |
| 23% | 18.4% | 1217 | 17.25% | 763 | 16.1% | 518 | 14.95% | 372 | 13.8% | 278 |
| 24% | 19.2% | 1153 | 18.0%  | 723 | 16.8% | 491 | 15.6%  | 353 | 14.4% | 264 |
| 25% | 20.0% | 1094 | 18.75% | 686 | 17.5% | 466 | 16.25% | 335 | 15.0% | 250 |

The shaded area represents the range of event rates and risk reductions that will be achieved given the targeted enrolment of 615 patients required for follow-up angiography, to achieve power of 80% in the surgical arm (two-tailed alpha of 0.05).

**Table 2b:** Sample Size Estimates for Primary Endpoint (Pharmacological Arm) – 1-Year Graft Occlusion (two-tailed  $\alpha=0.05$ ,  $\beta=0.20$ )

| Control Event Rate | Relative Risk Reduction |             |                      |             |                      |             |                      |             |                      |             |
|--------------------|-------------------------|-------------|----------------------|-------------|----------------------|-------------|----------------------|-------------|----------------------|-------------|
|                    | 15%                     |             | 20%                  |             | 25%                  |             | 30%                  |             | 35%                  |             |
|                    | Fish Oils Event Rate    | Sample Size | Fish Oils Event Rate | Sample Size | Fish Oils Event Rate | Sample Size | Fish Oils Event Rate | Sample Size | Fish Oils Event Rate | Sample Size |
| 20%         | 17.0%                   | 2629 | 16.0%                | 1447 | 15.0%                | 906  | 14.0%                | 615  | 13.0%                | 441* |
| 22%         | 18.7%                   | 2336 | 17.6%                | 1287 | 16.5%                | 806  | 15.4%                | 547  | 14.3%                | 393* |
| 24%         | 20.4%                   | 2091 | 19.2%                | 1153 | 18.0%                | 723  | 16.8%                | 491* | 15.6%                | 353* |
| 26%         | 22.1%                   | 1884 | 20.8%                | 1040 | 19.5%                | 652  | 18.2%                | 444* | 16.9%                | 319* |
| 28%         | 23.8%                   | 1707 | 22.4%                | 943  | 21.0%                | 592  | 19.6%                | 403* | 18.2%                | 290* |
| 30%         | 25.5%                   | 1554 | 24.0%                | 859  | 22.5%                | 540* | 21.0%                | 367* | 19.5%                | 264* |
| 32%         | 27.2%                   | 1419 | 25.6%                | 785  | 24.0%                | 494* | 22.4%                | 337* | 20.8%                | 242* |
| 34%         | 28.9%                   | 1300 | 27.2%                | 720  | 25.5%                | 453* | 23.8%                | 309* | 22.1%                | 223* |
| 36%         | 30.6%                   | 1195 | 28.8%                | 663  | 27.0%                | 417* | 25.2%                | 285* | 23.4%                | 206* |
| 38%         | 32.3%                   | 1101 | 30.4%                | 611  | 28.5%                | 385* | 26.6%                | 263* | 24.7%                | 190* |
| 40%         | 34.0%                   | 1016 | 32.0%                | 564  | 30.0%                | 356* | 28.0%                | 244* | 26.0%                | 176* |

The sample sizes noted with an asterisk (\*) represents the range of event rates and risk reductions that will be achieved for the pharmacological arm, given the targeted enrolment of 540 patients required for follow-up to achieve power of 80% (two-tailed alpha of 0.05). The sample sizes included in the shaded region represent the range of event rates and risk reductions that will be achieved for the pharmacological arm, given enrolment of 615 patients/arm planned for the surgical arm.

## 9 STUDY ORGANIZATION

### 9.1 Coordinating Centre

The trial will be conducted internationally and coordinated at the Population Health Research Institute (PHRI) at McMaster University and Hamilton Health Sciences, Hamilton Canada.

### 9.2 National Coordinators

Within each country, there will be a National Coordinating Office headed by an expert in cardiovascular disease and/or clinical trials. These units will be responsible for obtaining the national regulatory approvals, coordination of research ethics application at each site, organization

of training and follow-up meetings, dealing with other issues related to recruitment, data quality, and ensuring high rates of follow-up. All the National Coordinators along with the Operations Committee will serve on the Study Steering Committee, which will meet at least every 3 to 4 months by telephone or in person. The Steering Committee will be consulted regarding major decisions about the study.

### **9.3 Event Adjudication Committee**

The Events Adjudication Committee will blindly evaluate all primary outcome events using standardized definitions, along with supporting documentation. Members of the Events Adjudication Committee will be chosen based on their clinical expertise. All event adjudication will be blinded to treatment group.

## **10 ETHICAL AND REGULATORY STANDARDS**

### **10.1 Regulatory and ethical considerations**

Prior to initiation of a study site, the Study Sponsor, will obtain approval from the appropriate regulatory agency to conduct the study in accordance with applicable country-specific regulatory requirements. The study will be conducted in accordance with all applicable regulatory requirements.

The study will be conducted in accordance with Good Clinical Practice (GCP), all applicable subject privacy requirements, and the guiding principles of the declaration of Helsinki, including, but not limited to:

- Institutional Review Board (IRB)/Independent Ethics Committee (IEC) review and approval of study protocol and any subsequent amendments.
- Subject informed consent.
- Investigator reporting requirements.

### **10.2 Laws and regulations**

This study will be conducted in accordance with laws and regulations of the countries in which the trial is performed, as well as any applicable guidelines.

### **10.3 Informed consent**

It is the responsibility of the Investigator to obtain informed consent in compliance with national requirements from each subject prior to entering the trial or, where relevant, prior to evaluating the subject's suitability for the study.

The informed consent document used by the Investigator for obtaining subject's informed consent must be reviewed and approved by PHRI prior to Ethics Review Committee or similar body (IRB, REB) submission.

#### **10.4 Ethics Review Committee**

The Investigator must submit this protocol to an Ethics Review Committee or a similar body (IRB, REB) and is required to forward a copy of the written approval/advice signed by the Chairman to the Sponsor.

On the approval/advice sheet, the trial (SUPERIOR SVG – 2011-06-13), the study documents (protocol and informed consent material) and the date of the review should be clearly stated.

Drug supplies will not be released and the trial will not start until a copy of this written approval/advice has been received by PHRI.

